##### Time domain

For analysis of HRV in the time domain, the Mean RR, SDNN, and rMSSD [59–62] indices will be used. The Mean RR index corresponds to the means of all RR intervals [58, 59]. The SDNN index represents the standard deviation of all normal RR intervals recorded in a time interval, expressed in milliseconds (ms), and is considered a measure of global variability, that is, it evaluates both sympathetic and parasympathetic modulation [58, 59]. The rMSSD index corresponds to the root mean square of the differences between adjacent normal RR intervals in a time interval expressed in ms and assesses the behavior of parasympathetic autonomic modulation [6, 58].

##### Frequency domain

In the frequency domain, the following will be used: the low-frequency spectral component (LF — frequency between 0.04 and 0.15 Hz) index that evaluates the sympathetic and parasympathetic behavior, with sympathetic predominance and the high-frequency component (HF — frequency between 0.15 and 0.4 Hz), which is related as a marker of vagal modulation, in normalized units (nu) and in milliseconds squared (ms^2^) [58, 59]. The spectral indices will be calculated from a tachogram using the fast Fourier transform (FFT) algorithm [58, 59].

##### Poincaré plot

The Poincaré plot indices, SD1 and SD2, will be used for a quantitative analysis [59]. The Poincaré plot represents a time series within a Cartesian plane which allows each RR interval to be correlated with the previous interval. It is a geometric method for analysis in which each point is represented on the *x*-axis (horizontal/abscissa) by the preceding normal RR interval, and on the *y*-axis (vertical/ordinate) by the following RR interval [58, 59]. SD1 represents the dispersion of points perpendicular to the line of identity and appears to be an index of instantaneous recording of beat-to-beat variability, representing vagal modulation [58, 59]. SD2, on the other hand, represents the dispersion of points along the identity line and represents the HRV in long-term records, considered a marker of sympathetic and parasympathetic modulation [58, 59, 63].

##### Vagal reentry

Series of RR intervals of the last 30 s of all moments (M1–M11) will be selected in order to compare the moments and assess vagal reentry, as observed in the studies by Imai et al. [64] and Goldberger et al. [65].

### Sample size

The sample size calculation was based on the study by Schliessbach et al. [66], using the CPM test variable. The software G*Power 3.1.9.4 and a reference value of 98 ± 103 kPa were used, using a two-tailed hypothesis test with a test power of 80% and a significance level of 5%. Eventually, 19 participants per group were stipulated. A possible sample loss of 15% was considered so three participants will be added to each group, totaling 44 individuals divided into two groups (22 participants per group).

### Statistical analysis

Statistical analysis will be conducted using SPSS software (version 18; SPSS Inc. Chicago, IL, USA). Data normality will be verified by the Kolmogorov–Smirnov test, if normality is detected, the sample characterization variables will be presented as mean and standard deviation/ if not, in median and interquartile range. To compare the characterization of the sample, Student’s *t* test will be used for independent samples.

Descriptive data of outcomes will be presented in mean, standard deviation, and confidence interval values. Comparisons of outcomes between the groups studied and the moments will be performed using Generalized Linear Mixed Models adjusted to the data with Bonferroni post-test when the main analyzes are significant. In addition, the effects of the groups studied will be verified for all outcomes evaluated by calculating the effect size (ES) through Cohen’s *d*, which will be considered as “null” (< 0.2), “small” (≥ 0.2), “moderate” (≥ 0.6), “large” (≥ 1.2) or “very large” (≥ 2.0) [67]. Intention to treat will be used and, for data imputation, a mixed linear model will be used.

To correlate CPM and cardiac autonomic modulation, the Pearson or Spearman correlation test will be used according to the normality of the data. According to the parameters of Portney and Watkins [68], the correlation magnitude of 0.00 to 0.19 is considered to be very weak; 0.20 to 0.39 weak correlation; 0.40 to 0.69 moderate correlation; 0.70 to 0.89 strong correlation and 0.90 to 1.00 very strong correlation [68]. All analyses will assume a significance level of *p* < 0.05.

The external evaluator will enter the data into the database for screening, randomization, and statistical analysis. Dual data entry in electronic format will be used. Data integrity will be monitored regularly by examining data files for omissions and errors. Participants will receive an anonymous study ID to protect confidentiality, and only study investigators will have access to the final study dataset. The spreadsheets containing the raw numerical data of the data generated in this study will be stored in their entirety initially on two external hard drives and two online clouds. Any data needed to support the protocol can be provided upon request.

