**Methods:**

Women more than 50 years with knee osteoarthritis diagnosed according to the American College of Rheumatology criteria in the postmenopausal period will be considered eligible. The study will have blind randomization, be placebo-controlled, and be balanced in a 1:1 ratio. The total of 44 participants will be divided into two groups (22 participants per group): (i) remote ischemic conditioning and (ii) placebo remote ischemic conditioning. Protocol consisting of four cycles of total ischemia, followed immediately by four cycles of 5 min of vascular reperfusion, totaling 40 min. The primary outcomes in the protocol are conditioned pain modulation, which has the pressure pain threshold (kgf/cm^2^) as its primary outcome measure, and cardiac autonomic modulation, which has the indices found in heart rate variability as its primary outcome measure. Comparisons will be performed using generalized linear mixed models fitted to the data. For correlation, the Pearson or Spearman test will be used depending on the normality of the data. All analyses will assume a significance level of *p* < 0.05.

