### Study design

Data collection will be carried out at Sports Physiotherapy Laboratory at São Paulo State University (Unesp), School of Technology and Sciences, Presidente Prudente, São Paulo, Brazil. All procedures will be performed under standardized conditions (temperature: 21–23°C; relative humidity: 40–60%).

Each participant will attend the laboratory on two days separated by one week. On the first day they will be evaluated for anthropometric characteristics, using a scale (Tanita BC 554, Iron Man/Inner, Arlington Heights Illinois, USA) and a stadiometer (Sany—American Medical do Brasil, São Paulo, Brazil) and, later, the body mass index (BMI) will be calculated. Blood pressure measurements will also be performed [41] and the Knee Injury and Osteoarthritis Outcome Score (KOOS) questionnaire [42] will be applied. After these initial procedures, a 10 min rest will be performed and, in the sequence, the evaluation of total occlusion pressure (TOP) will be performed. After that, the initial CPM test will be performed, followed by the RIC, and finally the CPM test again. RR intervals will be captured from the initial 10 min of rest to the end of the complete CPM protocol.

On the second day, only the RR intervals will be captured before the RIC (15 min at rest), during, and after (15min at the end) the RIC. The study design is outlined in Fig. 2.

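### The group-by-moment analysis names no single between-arm contrast after RIC and no use of the pre-RIC value as a covariate, which leaves the treatment test open and can cost precision

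*Protocol article*

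**What the plan says.** The Statistical analysis section gives one sentence on the outcome comparison: "Comparisons of outcomes between the groups studied and the moments will be performed using Generalized Linear Mixed Models adjusted to the data with Bonferroni post-test". The post-tests follow when the main analyses are significant. The abstract describes the same models as fitted to the data, so the word 'adjusted' here refers to model fitting and not to covariate adjustment.

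Baseline is collected for both primary outcomes. For CPM, the Study design section states that "the initial CPM test will be performed, followed by the RIC, and finally the CPM test again" (CPM1 and CPM2). For HRV, the Cardiac autonomic modulation section lists the resting recording M1 on day 1 and the Pre-RIC recording on day 2 among the moments to be analysed.

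The Sample size section relies on CPM: "a reference value of 98 ± 103 kPa were used", two-sided 5% level, 80% power. It concludes: "Eventually, 19 participants per group were stipulated". Three per group are then added for loss, giving 22 per group.

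**The concern.** The question put to the trial is whether RIC differs from placebo after the intervention. That is one between-arm contrast, and it is estimated most precisely when the value measured before RIC is used as a covariate. The article treats the pre-RIC value as a level of the moment factor and does not say which term or contrast carries the treatment test.

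Two things are at stake. The first is precision: different contrasts from the same data have quite different power in a trial of this size. The second is interpretation. The post-tests are not limited to comparisons between arms. A pre-to-post test within the RIC arm and another within the placebo arm can be set side by side, but a significant result in one and not in the other is not a test of RIC against placebo.

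**Working it through.** **Inputs.** From the Sample size section: difference 98 kPa, SD 103 kPa, two-sided alpha 0.05, power 80%, 19 per group before loss. Assumed: 103 kPa is the SD of a single CPM value, equal at CPM1 and CPM2. Also assumed, because the document does not give it: the CPM1–CPM2 correlation rho, shown over a range.

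**Step 1: the plan's own figure.** The standardised difference is d = 98/103 = 0.951. A two-sample t test (noncentral t) has power 79.2% with 18 per group and 81.4% with 19. The stated 19 is reproduced. It corresponds to comparing one value per participant between arms, without using baseline.

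**Step 2: SD relevant to each contrast.**
- Post-RIC value alone: 103.
- Change, i.e. an unconstrained group-by-moment contrast over pre and post: 103 × √(2(1 − rho)).
- Baseline-adjusted (ANCOVA): 103 × √(1 − rho²), with one residual degree of freedom fewer (35 instead of 36).

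**Step 3: power for 98 kPa with 19 analysed per arm.**

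| rho | SD, change | Power, change | Power, post only | SD, adjusted | Power, adjusted |
|---|---|---|---|---|---|
| 0 | 145.7 | 52% | 81% | 103.0 | 81% |
| 0.3 | 121.9 | 67% | 81% | 98.3 | 85% |
| 0.5 | 103.0 | 81% | 81% | 89.2 | 91% |
| 0.7 | 79.8 | 96% | 81% | 73.6 | 98% |
| 0.8 | 65.1 | 99.5% | 81% | 61.8 | 99.7% |

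The adjusted variance divided by the change variance is (1 − rho²)/(2(1 − rho)) = (1 + rho)/2, which is 0.65, 0.75 and 0.85 at rho 0.3, 0.5 and 0.7. The confidence interval is narrower by 1 − √((1 + rho)/2), about 19%, 13% and 8%. The ratio is below 1 for every rho below 1. The change contrast is less precise than the post-RIC value alone when 2(1 − rho) > 1, that is, when rho is below 0.5.

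**Step 4: cost of adjustment when rho is zero.** Besides the lost degree of freedom, chance baseline imbalance inflates the variance by about 1 + 1/34 (34 = 2 × 19 − 4). With both allowed for, power at rho = 0 is 80.2%, against 81.4% unadjusted. At rho 0.3, 0.5 and 0.7 the same allowance gives 84%, 90% and 98%.

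**Step 5: within-arm tests, an illustration.** Suppose both arms shift equally by 0.4 SD, with no RIC effect, rho = 0.5 and 19 per arm. An unadjusted paired test has power p = 0.379 in each arm. Exactly one arm is significant with probability 2p(1 − p) = 2 × 0.379 × 0.621 = 0.47, and the RIC arm alone with probability 0.24. Bonferroni correction and the requirement of a significant main analysis would change these figures, but not what the tests compare.

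**The case against.** The strongest reply is that one sentence in a journal article neither specifies nor excludes an interaction term, a baseline covariate or a common baseline mean, and that such model terms may sit in an analysis plan that is not shown. This stands in part. A reader might infer that the trial will make no baseline adjustment at all, and the text does not support that. A group-by-moment term compares changes from baseline. A mixed model that keeps baseline as a moment but constrains the arm means to be equal there is about as efficient as ANCOVA. Keeping baseline as a moment is therefore not an error in itself. What remains is that the article does state its comparison, and as stated it covers several tests of unequal power.

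A reader might also infer that the trial is underpowered. That does not follow. The low figures need rho well below 0.5, which nothing in the document establishes. A between-arm comparison at the post-RIC moment fits the wording equally well and has the planned power. If 103 kPa is in fact the SD of a change, the change contrast has 81% power by construction and its column in the table does not apply.

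One could go further and read the group main effect, averaged over pre and post, as the treatment test; its power would be 42%, 38% and 34% at rho 0.3, 0.5 and 0.7. The article does not say this is the test.

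Finally, no sentence says that conclusions will rest on within-arm tests. The same section reports effect sizes for the groups, and the post-tests are Bonferroni-corrected and conditional on a significant main analysis. The within-arm point is therefore a risk left open, not a stated intention.

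**Conclusion.** The point holds as one of efficiency and of an unfixed treatment contrast. Arms are randomised, so none of the between-arm contrasts is biased, and the stated 19 per group is not wrong on this account.

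The size of the gain depends on two assumptions: that 103 kPa is the SD of a single CPM value, and the value of rho. Under the first, adjustment raises power over the change contrast by about 17, 9 and 2 percentage points at rho 0.3, 0.5 and 0.7 (85 − 67 is 17 before rounding: 84.8 − 67.4; then 90.9 − 81.4 and 97.9 − 95.8). Over a post-RIC comparison alone the gain is about 3, 9 and 16 points (84.8, 90.9 and 97.9 less 81.4). Adjustment is not costless at every rho: near zero it loses about one point. At rho of 0.5 or more the change contrast still reaches the planned 80%, so the case for the fix there is precision and clarity, not rescue of the planned power.

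**What to change.** State the primary CPM analysis as the between-arm difference in CPM2 with CPM1 as covariate, or as a mixed model with arm means constrained equal before RIC, reported with a 95% CI. For each HRV index use its own pre-RIC value in the same way, and name which pre-RIC recording serves on day 1. Base conclusions about RIC on these contrasts. Label within-arm and moment-by-moment post-tests descriptive, because they do not test RIC against placebo.

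No new data are needed, since every covariate is already collected. The cost is a change of wording and one degree of freedom, with a negligible loss of power if rho is near zero.

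### The stated 80% power belongs to one ungated two-sample test on CPM at 5%, but the analysis section prescribes a mixed model followed by a Bonferroni post-test only if the model is significant

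*Protocol article*

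**What the plan says.** The Sample size section bases the calculation on CPM ("using the CPM test variable"). The settings are described as "using a two-tailed hypothesis test with a test power of 80% and a significance level of 5" per cent. For the effect and its spread, the section says that "a reference value of 98 ± 103 kPa were used". The result is given as "Eventually, 19 participants per group were stipulated", and the allowance for loss follows: "A possible sample loss of 15% was considered so three participants will be added to each group, totaling 44 individuals". The type of test is not named. Allocation is "balanced in a 1:1 ratio".

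The Statistical analysis section says that outcomes are compared between groups and moments, and that this is "performed using Generalized Linear Mixed Models adjusted to the data with Bonferroni post-test when the main analyzes are significant". The level for all analyses is 5%.

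Under Study design, CPM is measured twice on the first day: "the initial CPM test will be performed, followed by the RIC, and finally the CPM test again". For CPM the layout is therefore two groups by two moments. The article does not say which model term opens the post-test, how many comparisons share the Bonferroni correction, or which contrast decides the CPM result.

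**The concern.** The power statement and the analysis rule do not describe the same test. The sizing is for one comparison at 5% that does not depend on any other result. The analysis section puts a significant model result in front of the pairwise comparisons and then tests them at a reduced level. Both steps can only lower the chance that a given pairwise comparison succeeds.

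CPM is one of the primary outcomes and the only variable used for sizing. If the assumed effect is real but the RIC-versus-placebo comparison fails a gate or a reduced level, the null result would be read as coming from a trial with 80% power. If nobody has fixed which test decides, that can also be settled after the results are known.

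**Working it through.** **Inputs.** From Sample size: 98 and 103 kPa, read as the between-group difference and the SD, so d = 98/103 = 0.951; two-sided 5%; 19 per group, 22 after the allowance for loss. From Study design: two CPM moments, called CPM1 and CPM2. Assumed, because not given: number of comparisons m, gate term, and correlation ρ between CPM1 and CPM2 (equal SDs).

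**Step 1: reproduce the stated figure.** The power of a two-sample t test is P(|T| > t[1 − α/2; 2n − 2]), where T is noncentral t with noncentrality d√(n/2). For n = 19 the noncentrality is 0.951 × √9.5 = 2.93 on 36 df.
- n = 18: 79.2%; n = 19: 81.4%. So 19 is the smallest n that reaches 80%.
- A paired or one-sample t test would give 11, and a one-sided two-sample test 15. Neither gives the 19 per group.

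**Step 2: Bonferroni alone.** Same formula with α = 0.05/m and no gate. No correlation is needed.

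| m | 19 per group | 22 per group | n per group for 80%, before loss |
|---|---|---|---|
| 1 | 81.4% | 86.9% | 19 |
| 2 | 72.2% | 79.4% | 23 |
| 4 | 62.1% | 70.5% | 27 |
| 6 | 56.1% | 65.0% | 29 |

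Six is the number of pairs among the four group-by-moment cells. A gate can only lower these figures, so they are ceilings.

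**Step 3: gate plus Bonferroni.** Simulation of the 2 × 2 layout, 60,000 runs per setting, effect on CPM2 in the RIC arm only. The gate is the group-by-moment interaction at 5% (a t test on the change). The post-test is the group difference in CPM2 at 0.05/m. With 19 per group:

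| ρ | m = 1 | m = 2 | m = 4 | m = 6 |
|---|---|---|---|---|
| 0 | 50% | 48% | 44% | 41% |
| 0.5 | 70% | 64% | 56% | 51% |
| 0.9 | 81% | 72% | 62% | 56% |

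With 22 per group the range over ρ from 0 to 0.9 is 55% to 79% for m = 2 and 49% to 65% for m = 6.

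Other gates, 19 per group, m = 2 to 6: 56% to 72% if any significant model term suffices, and 31% to 48% if only the group main effect does. That main effect averages CPM2 with the pre-treatment CPM1 and so halves the difference.

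**Step 4: the interaction as the deciding test.** With equal SDs σ, the change has SD σ√(2(1 − ρ)), so the standardised effect is d/√(2(1 − ρ)). At ρ = 0.5 the root equals 1, the effect is again 0.951, and power is 81.4%. The same holds at any ρ if 103 kPa is already the SD of the change. If it is the SD at each moment, power is about 52% at ρ = 0, 67% at ρ = 0.3 and 96% at ρ = 0.7.

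**The case against.** The strongest reply is that the post-test is a follow-up and the model is the main analysis. With two groups and two moments the interaction has one degree of freedom and answers the treatment question alone. On that reading no Bonferroni loss arises, and the stated power is kept under the conditions in step 4. This stands as a possible reading. But the article does not name the interaction as the deciding test, and the power then depends on a correlation, or a reading of 103 kPa, that it does not state.

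A related reply is that there is only one group contrast per moment, so m = 1. That removes the division, but a gate would remain: with the interaction as gate, power is 50% to 81% depending on ρ.

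Analysis by intention to treat with imputation could bring the analysed number towards 22. That helps, but a post-test split over two comparisons still reaches at most 79%.

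It can also be said that contrasts and covariance assumptions belong in a fuller plan. The point here is not the missing detail, however: both the 80% and the gated rule are printed, and they do not match. The label of exploratory under Trial design softens the consequence but does not remove the mismatch.

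A reader might go further and infer that the trial has 41% to 72% power under its own inputs, or that 80% holds only with ρ of about 0.7 or more and a single comparison. The documents support neither. The range needs m, a gate term and ρ, none of which the article gives; other gates and 22 per group give other ranges. The second inference is contradicted by the interaction test, which reaches about 81% at ρ = 0.5.

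**Conclusion.** The point holds as a mismatch between two printed statements. The 80% is the power of one ungated two-sample test at two-sided 5%. The written procedure is a mixed model with a conditional Bonferroni post-test, and the sizing makes no allowance for either step. It is certain that the two differ; the loss of power is conditional. It arises if the RIC-versus-placebo conclusion rests on a post-test split over two or more comparisons, where the ceiling at 19 per group is 72%, before any gate. All figures take the 98 kPa difference and 103 kPa SD as true, and say nothing about whether that effect is realistic for RIC. The change is worth making because it is nearly free and CPM is the outcome on which the trial is sized.

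**What to change.** In Statistical analysis, name one deciding RIC-versus-placebo contrast for CPM: the group difference after RIC, estimated from the mixed model and preferably adjusted for the CPM value before RIC, which is already collected. Adjustment costs about one degree of freedom if ρ is zero and gains precision otherwise, since the residual variance falls by the factor 1 − ρ². Test this contrast once at two-sided 5%, not conditional on another model test and not divided by Bonferroni. Because the Outcomes section measures several knee sites and the hand, and defines both an absolute and a percentage CPM, the sentence must also name one site or summary and one metric.

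Keep the gated Bonferroni post-tests for the other between-moment and within-group comparisons, labelled secondary.

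If the gated rule is to remain the deciding test for CPM, replace the 80% in Sample size with the power of that rule, and state the gate term, the number of comparisons and the assumed correlation.

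The cost is one or two sentences, with no added participants or measurements. The downside is that the other pairwise comparisons become secondary or, under the alternative, that the stated power looks less favourable.

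### The separate mixed-model imputation step has no stated way to carry imputation uncertainty; if filled-in values count as observed, the 5% test runs at roughly 6% to 10% at the planned loss

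*Protocol article*

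**What the plan says.** The Statistical analysis section of the protocol article names the main analysis: "Comparisons of outcomes between the groups studied and the moments will be performed using Generalized Linear Mixed Models adjusted to the data", followed by Bonferroni post-tests. After the effect-size plan it adds, as a separate statement, "Intention to treat will be used and, for data imputation, a mixed linear model will be used". The error level is fixed for everything: "All analyses will assume a significance level of *p* < 0.05".

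The Sample size section anticipates missing participants: "A possible sample loss of 15% was considered so three participants will be added to each group, totaling 44 individuals divided into two groups", that is, 22 per group.

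The article does not state whether imputation is single or multiple, whether a random residual is added to the predictions, or whether the completed values enter the comparison as if they had been measured.

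**The concern.** Two models are named for two jobs: one fills in missing outcomes, the other compares the groups. If the first produces one value per gap and the second treats that value as data, the comparison counts participants who contributed no measurement. The residual variance is then too small and the sample size too large, so standard errors shrink and the test rejects too often.

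The step is also redundant. A mixed model fitted by likelihood already uses every observed moment from each randomised woman. Filling gaps from a similar model adds no information beyond what those observations hold.

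At stake are the confidence intervals and the nominal 5% level for the RIC versus placebo contrast in a trial of 44 women. Missing values are foreseeable:
- Some HRV recordings fall on a second visit a week later (Study design).
- RR series that fail the sinus-beat criterion are not used (Cardiac autonomic modulation).
- A session stopped early for symptoms (Adverse event reporting and harms) may leave post-RIC values missing.

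**Working it through.** **Inputs.** From Sample size: reference value 98 ± 103 kPa, two-sided 5%, 80% power, 19 per group before loss, 3 added, 22 enrolled per group. From Statistical analysis: mixed-model comparison by group and moment at 0.05. Not in the article, and therefore assumed: the correlation between a woman's pre- and post-RIC values, taken from 0 to 0.9; and values missing at random.

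**The plan's own figure.** The standardised effect is 98/103 = 0.951. A two-sample, two-sided t-test needs 18.35, so 19 per group (power 81.4%). Then 15% × 19 = 2.85, rounded to 3, gives 22. The stated size is reproduced. Three lost of 22 is 3/22 = 13.6%.

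**Closed form, whole before/after contrast imputed.** With two moments and equal groups, the group-by-moment test equals a t-test on the changes. Let n = 22 − m be observed per group, and let m be filled at the group mean. Filled values add nothing to the residual sum of squares, but it is divided by 42 instead of 2(n − 1), and the mean is treated as resting on 22 instead of n:

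reported SE / correct SE = √{[2(n − 1)/42] × [n/22]}

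- m = 3, n = 19: √[(36/42) × (19/22)] = √(0.857 × 0.864) = 0.860. The critical value from t on 42 df is 2.018. Multiplied by 0.860 it is 1.736, which on t with 36 df gives a true error of 9.1%.
- m = 3.3 (exactly 15%), n = 18.7: ratio 0.846, error 9.6%.
- m = 4, n = 18: ratio 0.814, error 11.0%.

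**Simulation under the null, 22 per group, 3 missing per group, group-by-moment test.** Whole-contrast rows use 40,000 replicates; post-only rows use 8,000, with Monte Carlo error of about √(0.08 × 0.92/8,000) = 0.3 percentage points.

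| What is missing | How it is handled | Type I error |
|---|---|---|
| Whole contrast | Model mean, counted as observed | 9.1% |
| Whole contrast | One random draw, counted as observed | 8.6% |
| Post value only | Group mean at that moment | 6.4–6.8% |
| Post value only | Predicted from the pre value; correlation 0 / 0.5 / 0.9 | 6.9% / 7.9% / 9.0% |
| Post value only | Prediction plus one random residual | 6.9–8.0% |
| Whole contrast | Multiple imputation, 20 sets, Rubin's rules | 4.7% |
| Whole contrast | Observed data only, no imputation | 4.7% |

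Adding a random residual once does not cure the problem; only pooling over several imputations, or not imputing, does. If the groups are compared at the post moment alone, with the post value filled by group mean or prediction, the error is 5.8–9.4%.

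An ANCOVA on the pre value, which is not the planned model, gives 9.6–9.8% with 15% of post values filled by prediction and 4.7–5.0% on the observed values.

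**Smaller losses.** With the whole contrast imputed at the mean, 1 of 22 lost per group gives 6.1% and 2 of 22 gives 7.5%.

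**The case against.** The strongest reply is that the article does not describe the faulty procedure. It names a model for imputation and nothing more. The sentence joins imputation to intention to treat, so it may be loose wording for keeping all randomised women and letting the mixed model handle gaps by likelihood. It may equally mean multiple imputation from a mixed model. Under either reading the error stays near 5%. Details such as the number of imputations and pooling are often left to a full protocol or analysis plan, which is not shown. The trial also calls itself exploratory (Trial design).

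Much of this stands. The inflation follows from one permitted reading, not from a rule the article fixes. The 15% is an allowance for lost participants, not a documented rate of missing outcomes. Both CPM tests fall within the same visit (Study design), so CPM may lose fewer values. The Eligibility criteria section also says that women who withdraw or whose RR capture fails will be excluded, so how many outcomes would be imputed is unclear.

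What does not stand is that this is merely an omitted detail. The article commits to an imputation step, names its model and sets it apart from the comparison model. A reader who follows that wording literally may fill in once and analyse the completed data.

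**Conclusion.** The point holds conditionally. The plan contains a separate imputation step with no stated route for its uncertainty into the standard errors, and its wording permits single imputation analysed as observed data. If that is done with 3 of 22 missing per group, the nominal 5% group-by-moment test runs at roughly 6% to 10%: about 9–10% with whole contrasts imputed, about 6–9% with only post-RIC values imputed.

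A reader might infer that the trial will run at about twice its stated error rate on both primary outcomes. The article does not support that. Nothing in it says imputed values count as observed. The top of the range needs the full planned loss and, for the planned test, either whole contrasts imputed or a high pre/post correlation. The calculations also use two moments and a normal outcome, not the many-moment HRV series.

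The range rests on missingness at random, equal loss in both groups and the assumed correlations. The sentence is worth correcting before analysis because the redundant step can only leave the error rate alone or harm it.

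**What to change.** Replace the imputation sentence with wording such as: *the planned mixed model will be fitted by (restricted) maximum likelihood to all observed outcomes of all randomised women, analysed as randomised, without prior imputation.* If imputation is kept, make it a sensitivity analysis by multiple imputation with standard errors pooled by Rubin's rules. In the same edit, reconcile the post-randomisation exclusions in Eligibility criteria with the intention-to-treat statement, since they decide which outcomes count as missing.

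The cost is one sentence and less analysis work, with no extra participants or visits. Confidence intervals become somewhat wider than under single imputation. With 3 of 22 whole contrasts missing per group, the standard error rises by a factor of 1/0.860 = 1.16; with fewer missing values the change is smaller.
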